**[name]**

**[name]**

**[name]**

**Randomized controlled trial study protocol**

**September 2011**

**Background**

Diarrhoea is the leading cause of morbidity and mortality, especially among children under five years of age in developing countries. The World Health Organisation (WHO) estimates that there are approximately 2.5 billion episodes and 1.5 million (nearly one in five) deaths annually in children under-five years of age which accounts for 21% of all deaths in developing countries. It kills more young children than Acquired Immunity Deficiency Syndrome (AIDS), malaria and measles combined. Africa and South Asia are home to more than 80 percent of child deaths due to diarrhoea (Black *et al*., 200; Parashar *et al*., 2003; UNICEF/WHO 2009).

Lack of access to safe drinking water is a major cause of diarrhoeal diseases. The Millennium development goal (MDGs) calls for reducing by half theproportion of people without sustainable access to safe drinkingwater. World health organization estimates that there are 1.1 billion people without access to safe drinking water. Progress towards this target is indicated by the proportion of households reporting the use of improved water source. However,research worldwide has shown that even drinking water which is safe at the source is subject to frequent and extensive faecal contamination during collection, storage and use in the home (Wright *et al*, 2004; James, 2005; Andrew, 2008; Othero *et al*., 2008).

To reduce this problem, point-of-use water treatment has been advocated as a means to substantially decrease the global burden of diarrhoea and to contribute to the MDGs. Point- of- use water treatment is the treatment of water at the household level to reduce the contamination of water at the source, during transport and storage. These include chlorination, filtration, solar disinfection, combined flocculation and disinfection, boiling and improved storage. Evidence on health outcome trials suggests that household water treatment (HWT) may reduce diarrhoea by 30-40%. However, There is large heterogeneity of effect estimates (Clasen *et al*., 2006; UNICEF/ WHO 2009).

Among the household water treatment options household-based chlorination is the most cost-effective where resources are limited, yielding high returns on every dollar invested mainly from lower health care costs but also from increased productivity and school attendance (Hutton, 2007; Clasen, 2007). It is promising approaches to supply safe water at the household level. Disinfection of water with chlorine and safe storage has resulted in significantly improving the microbial quality and reducing diarrheal disease (Semenza, 1998; Quick, 1999; Reller, 2003; Luby, 2004; Crump, 2005) The health impact gained from promoting point-of-use water treatment and safe storage varies considerably from one community to another and depends on a variety of technology-related as well as site-specific environmental and demographic factors. The gains for some communities may be very significant while for others may be relatively modest (Sobey, 2002; Thompson, 2003).

However, many researches are suggesting that much of the current apparent evidence for the effect of HWT may be strongly biased and that without other environmental improvements the benefits of HWT may be negligible (Kirchhoff, 1985; Eisenberg, 2000*;* Jain 2008; Schmidt, 2009). The limitations of current effect estimates due to responder and observer bias have been indicated by literatures (Arnold and Colford, 2007; Clasen *et al*., 2006; Fewtrell *et al*., 2005).

Based on the evidence it recommended the need for more research to identify the actual contribution that the intervention can make in preventing diarrhoea under different conditions, and not to overstate the effect due to bias. There are many unanswered questions about HWT especially with regard to effectiveness, acceptability in poor communities and identifying suitable target populations. Further development, implementation, evaluation and comparisons of household water treatment and safe storage technologies is both justified and encouraged (Thompson, 2003; Clasen, 2009; Schmidt, 2009).

Therefore this research will be conducted in to determine the acceptability and effectiveness of household water chlorination in reducing diarrhea episode and increasing weight gain among under-five children.

**Objective of the study**

**Primary objective:** To assess the effectiveness of household water chlorination in reducing the prevalence and incidence of diarrhea among under-five children

**Secondary objective:**

1. To determine the effectiveness of household water chlorination in increasing weight gain among under-five children.
2. To determine the acceptability of household water chlorination among the intervention households

**Study design and setting:** A community based randomised field trial will be conducted to determine the acceptability and effectiveness of household water disinfection with chlorine on reducing the prevalence and incidence of diarrhea and weight gain among under-five children in randomly selected clusters of Kersa Demographic and Health Research Centre field site. The study area has a population of 47,036 distributed among the 10 kebeles of which 7870 are children under-five years of age. All the households do not have running water. Families walk to collect water from springs, streams, or wells. The study will be conducted for a 16-weeks period from June to August 2011.

**Sample size**

The sample size is calculated using methods published by Hyes and Bennett (Hyes 1999). It is assumed that 11% incidence of diarrhea among children under-five years of age (baseline survey), 80% power, 10% drop out, 95% confidence interval and design effect of three from clustering. We calculated 18 clusters, 24 children under the age of five years per cluster will be followed for 16 weeks to detect 40% reduction in the incidence of diarrhea between the intervention and control groups.

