**Outcomes:**

Primary outcome for this study is the occurrence of diarrhea among under-five children. Diarrhoea is defined as three or more loose or watery stools in 24 hours. Diarrhea is considered as new episode if it occurred after a period of three diarrhea free days (Morris 1994, Wright 2006). Incidence will be calculated as the number of new episodes divided by the total number of person–weeks observation and longitudinal prevalence as the number of weeks of diarrhea divided by the total number of weeks of observation for each child ( Morris 1996, Schmidt 2011) .

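### The 11% planning incidence has no time unit, and the stated inputs do not return 18 clusters of 24 per arm at 80% power on either main reading

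*Protocol*

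**What the plan says.** The Sample size section gives its inputs as follows: "It is assumed that 11% incidence of diarrhea among children under-five years of age (baseline survey), 80% power, 10% drop out, 95% confidence interval". It does not say whether the 11% is per week, per recall period or over the whole follow-up. It adds a "design effect of three from clustering". The target is "to detect 40% reduction in the incidence of diarrhea between the intervention and control groups".

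The result is stated as "We calculated 18 clusters, 24 children under the age of five years per cluster will be followed for 16 weeks". The flow chart under Enrolment and randomization shows 18 clusters and 432 children in each arm, so the 18 is per arm.

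The Outcomes section fixes the unit of the outcome, though not of the planning value: "Incidence will be calculated as the number of new episodes divided by the total number of person–weeks observation". Diarrhoea is recorded weekly (Diarrhoea monitoring), and the flow chart counts observation in person-weeks.

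**The concern.** A sample size for a rate needs a rate, and a percentage without a period is not one. The 11% comes from a baseline survey, and no passage ties it to the person-week in which the outcome is measured. The same gap affects the design effect: the protocol does not say whether the 3 applies to children or to person-weeks, and it gives neither an intracluster correlation nor a between-cluster coefficient of variation.

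The section reads as a complete derivation, yet the inputs do not lead to the result on either of the two readings that come first to mind, and the two miss in opposite directions. This is the only power statement for the primary outcome. A reader cannot tell from it whether the trial was planned with a wide margin or a thin one, or which reduction it could reasonably be expected to detect.

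**Working it through.** **Inputs.** From the Sample size section: control value 0.11, intervention value 0.6 x 0.11 = 0.066, power 80%, drop-out 10%, design effect 3, 24 children per cluster, 16 weeks. From the flow chart: 18 clusters per arm. A two-sided 5% test is assumed from the 95% confidence interval. Then (1.96 + 0.8416)² = 7.849.

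**Size of the stated design.** 18 x 24 = 432 children per arm; 432 x 16 = 6,912 person-weeks (the flow chart has 6,921). After 10% drop-out: 388.8 children or 6,221 person-weeks. Divided by the design effect: 129.6 effective children or 2,073.6 effective person-weeks per arm.

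**Reading A: 11% is a rate per person-week.**
- Person-weeks per arm = 7.849 x (0.11 + 0.066) / 0.044² = 713.5. Times 3 = 2,141; divided by 0.9 = 2,378.
- One cluster supplies 24 x 16 = 384 person-weeks, so 2,378 / 384 = 6.2 clusters, against 18 stated.
- Power of the stated design: SE = √(0.176 / 2,073.6) = 0.00921; 0.044 / 0.00921 = 4.776; Φ(4.776 − 1.96) = 99.8%.
- Smallest relative reduction r at 80% power solves 0.11 x 2,073.6 x r² = 7.849 x (2 − r), so r = 0.246, about 25%.

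**Reading B: 11% is a proportion of children, one yes/no per child.**
- Children per arm = 7.849 x (0.11 x 0.89 + 0.066 x 0.934) / 0.044² = 647. Times 3 = 1,940; divided by 0.9 = 2,156, or about 90 clusters of 24.
- Power of the stated design: SE = √(0.1595 / 129.6) = 0.0351; 0.044 / 0.0351 = 1.254; Φ(1.254 − 1.96) = 24%.
- Variants do not rescue it. The pooled formula gives 2,167 per arm, a continuity correction 2,317 and a one-sided test 1,707. Dropping the design effect altogether gives 58% power (63% without drop-out).

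**Other units, same rate formula, design effect 3.**

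| 11% refers to | Control rate per week | Person-weeks needed per arm | Clusters of 24 | Power at 18 x 24 |
|---|---|---|---|---|
| 1 week | 0.110 | 2,378 | 6.2 | 99.8% |
| 2 weeks | 0.055 | 4,757 | 12.4 | 92% |
| 3 weeks | 0.0367 | 7,135 | 18.6 | 79% |
| 4 weeks | 0.0275 | 9,514 | 24.8 | 67% |

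The power is 80% at a unit of about 2.9 weeks (0.038 per week). The document names no such period.

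**Clustering expressed as a between-cluster coefficient of variation k, weekly reading.** With y = 24 x 16 x 0.9 = 345.6 person-weeks per cluster, a standard formula for comparing cluster-level rates is c = 1 + 7.849 x [(λ0 + λ1)/y + k²(λ0² + λ1²)] / (λ0 − λ1)².
- The design effect that corresponds to k is 1 + k² x (λ0² + λ1²) x y / (λ0 + λ1). At 0.11 and 0.066 a design effect of 3 gives k of about 0.25, and then c = 7.2 clusters.
- Setting c = 18 gives k = 0.47, with design effect 1 + 0.2239 x 0.016456 x 345.6 / 0.176 = 8.2, so about 8 rather than 3.
- Power with 18 clusters per arm is 99.6% at k = 0.25, 90% at 0.40, 80.5% at 0.47 and 76% at 0.50.

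The stated 3 means something different at child level: 3 = 1 + 23ρ gives an intracluster correlation of 0.087. The figure therefore cannot be carried from one unit to another unchanged.

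**The case against.** The strongest defence is that the design itself may be sound. The document consistently points to person-weeks: children are followed for 16 weeks, visited weekly, and incidence is defined per person-week. On that reading the trial is larger than its inputs demand. The child-level figure of 24% discards the repeated weekly observation and fits the protocol poorly. A recall period near three weeks would bring the stated 80% almost exactly into line. So would the weekly rate with stronger clustering, since k = 0.47 is a value that a planner might choose. All of this stands, and it limits the point.

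A reader might infer that the trial is underpowered, or that it lacks 80% power. The documents do not support that: the power depends on a unit they leave out, and the best-fitting unit gives far more than 80%. Nor can 99.8% be taken as established. It assumes that the design effect of 3 absorbs correlation between weeks in the same child as well as between children in a cluster. If it does not, 99.8% is an upper bound.

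It is also tempting to say that a baseline survey can yield only a prevalence. The protocol does not describe the recall, and the Baseline survey paragraph speaks of pre-intervention rates, so this is not established. Finally, a null result would not be beyond interpretation: its confidence interval would show which reductions are excluded, whatever power was planned.

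The defence does not supply the missing unit. Each reconciliation requires solving backwards for an unstated period, or replacing the stated design effect of 3 by about 8.

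**Conclusion.** The concern holds in this form: the stated 80% power cannot be reproduced or determined from the text. The inputs call for 6 to 7 clusters per arm on the person-week reading and about 90 on the child-proportion reading, against 18 stated. The power of the stated design runs from about 24% to above 99% across readings, with about 92%, 79% and 67% for units of 2, 3 and 4 weeks. On the best-supported reading it is about 99.8%, with a smallest detectable reduction of about 25%.

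These figures rest on a two-sided 5% test, independent Poisson person-time apart from the design effect, and 10% of person-time lost. The defect is in the derivation and its reporting. It does not show that 18 clusters of 24 is the wrong size. It still needs correcting, because it is the only justification given for the size of the trial.

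**What to change.** Rewrite the Sample size paragraph so that it:
- states the period to which the 11% refers, and converts it to episodes per child-week, the unit in the Outcomes section;
- states the clustering assumption on that same unit, preferably as an explicit between-cluster coefficient of variation with a range (0.25 to 0.5 would serve, declared as an assumption), and says whether it is meant to cover correlation between weeks in the same child;
- shows the formula with 24 x 16 x 0.9 = 345.6 person-weeks per cluster;
- keeps 18 clusters of 24 per arm, and restates the power for a 40% reduction and the smallest reduction detectable with 80% power across that range.

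The cost is a recalculation and one rewritten paragraph. No clusters, children or visits are added. The stated power will probably change.

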**Enrolment and randomization**

We will use cluster level randomization to avoid ethical concerns and minimize the potential transfer of the intervention between the two groups. Ethiopian population census enumeration area map will be used to identify the clusters. There are 64 clusters (enumeration area) in study site. We will randomly select 36 clusters to participate in the study. Cluster selection will be done by central statistics authority using simple random sampling. Households in the selected clusters with at least one child under the age of five year will be identified by census. This is because we are expecting higher prevalence and incidence of diarrhea and the effect of the intervention would be higher among this group. Twenty four children will be selected randomly from the each cluster for follow up. Assigning of the clusters in to the intervention and control group will done by independent person using random sampling technique. Field workers will approach selected households in each cluster for baseline survey.

64 clusters

Randomly selected

36 cluster

**Randomization**

**Intervention Control**

18 clusters, 432 children

18 clusters, 432 children

**Follow up Follow up**

6921 person week observation

Intention to treat analysis

6921 person week observation

Intention to treat analysis

**An**

**Baseline survey:** we will collect basic information including demographic and socioeconomic information, water sources and water handling practices, access and water quality, housing conditions, and pre-intervention diarrhea rates.

**Interventions:** The intervention for this study will be 1.25% Sodium hypochlorite solution locally branded as “watergauard”. The intervention household will receive the hypochlorite disinfectant for household water treatment while the control groups will continue their usual practice. Both the intervention and control households use Jerricans for water collection and storage. Local women will be selected for the distribution of the intervention (sodium hypochlorite). They will be trained on how to use sodium hypochlorite for household water treatment and explain to the intervention households how to treat water. The intervention will be distributed for 16 weeks.

**Outcomes:**

Primary outcome for this study is the occurrence of diarrhea among under-five children. Diarrhoea is defined as three or more loose or watery stools in 24 hours. Diarrhea is considered as new episode if it occurred after a period of three diarrhea free days (Morris 1994, Wright 2006). Incidence will be calculated as the number of new episodes divided by the total number of person–weeks observation and longitudinal prevalence as the number of weeks of diarrhea divided by the total number of weeks of observation for each child ( Morris 1996, Schmidt 2011) .

**Inclusion and exclusion criteria**

Inclusion criteria: Children under the age of five years will be included in the study.

Exclusion criteria: children who are seriously sick with other disease at the time of the study.

**Diarrhoea monitoring**

The survey instrument will be pre-tested and validated in the nearby villages. Field workers will use a validated questionnaire to record the occurrence of diarrhea in children under the age of five years, water treatment practices and residual chlorine in the selected households on weekly bases. A female caregiver will provide the information.

**Anthropometric measurement:** The secondary outcome for this study is weight gain. All fieldworkers will be trained on anthropometric measurement techniques over two days of training, and they will collect measurements in teams of two. Fieldworkers will measure the weight of children using digital scales. These scales will be calibrated every day before starting the data collection. Anthropometric measurement will be taken at the baseline and the end of the

Study.

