**Statistical analysis**

All the data will be double entered into EPI info. Intention- to- treat analysis will be applied to compare between the intervention and control groups. Mean will be calculated to determine the proportion of households who use the intervention. Generalized Estimation Equation (GEE) will be used to compare the prevalence and incidence of diarrhea between the intervention and control arms while T-test will be used to compare the mean weight gain between the two groups.

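### Weight gain in children from birth to under five is compared by an unadjusted t-test, leaving removable age variation in the error and the comparison exposed to age imbalance

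*Protocol*

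**What the plan says.** Under Anthropometric measurement (in the Diarrhoea monitoring section), the protocol states: "The secondary outcome for this study is weight gain". Two weighings are planned: "Anthropometric measurement will be taken at the baseline and the end of the" study.

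Under Statistical analysis, "Intention- to- treat analysis will be applied to compare between the intervention and control groups", and for weight a "T-test will be used to compare the mean weight gain between the two groups". No covariate and no age standardisation is named.

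Eligibility is wide: "Children under the age of five years will be included in the study", with no age strata. The Baseline survey collects demographic information, and baseline weight is measured, so age and starting weight should be to hand for each child.

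The Sample size section assumes "80% power, 10% drop out, 95% confidence interval and design effect of three from clustering". That calculation is for diarrhoea only (it is sized "to detect 40% reduction in the incidence of diarrhea between the intervention and control groups"). It gives 18 clusters of 24 children per arm. No standard deviation, effect or sample size is given for weight.

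**The concern.** A t-test on raw gain treats the difference in growth between a young infant and a four-year-old as noise. In a cohort that runs from birth to five years, that noise may be a large share of the total variance, and the data that would remove it are collected anyway. The result is a wider confidence interval than necessary for the only growth outcome in the trial.

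The second issue is balance. Gain exists only for children weighed twice. If the age mix of those children differs between arms, by chance or because loss takes different ages from each arm, the difference in raw means carries that age difference. An analysis without age has no means of correcting it.

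This is separate from the t-test's neglect of clustering. A cluster-adjusted comparison of raw gain would leave the same age variation in place.

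**Working it through.** **Children with both weights.** The protocol gives 18 × 24 = 432 children per arm and 10% drop-out. If that 10% applied to final weights, 432 × 0.90 = 388.8, so about 389 per arm would have a gain value and about 43 would not.

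**Share of variance due to age.** The documents give no age mix, gain by age or standard deviation, so these inputs are assumptions: 10%, 10% and 80% of children aged under 6, 6–11 and 12–59 months; mean 16-week gains of 2.5, 1.2 and 0.7 kg; within-age SD of 0.5 to 0.9 kg.

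- Mean gain: 0.1 × 2.5 + 0.1 × 1.2 + 0.8 × 0.7 = 0.93 kg.
- Between-age variance: 0.1 × 1.57² + 0.1 × 0.27² + 0.8 × 0.23² = 0.296, so SD 0.544 kg.
- Share of variance: 0.296 / (0.296 + 0.25) = 0.54, down to 0.296 / (0.296 + 0.81) = 0.27.

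**Precision, child-level part.** Removing that share multiplies the child-level standard error by √(1 − 0.54) = 0.68 to √(1 − 0.27) = 0.86 (unrounded shares give 0.677 and 0.856), a reduction of about 32% to 14%.

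**Precision, total.** Suppose the design effect of 3 held for weight (the protocol states it for diarrhoea). With 24 per cluster the intracluster correlation is (3 − 1) / (24 − 1) = 0.087. The variance of an arm mean is proportional to (1 − 0.087) + 24 × 0.087 = 0.913 + 2.087 = 3, so the child-level part is 0.913 / 3 = 0.304. If adjustment acts on that part alone:

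- √(1 − 0.304 × 0.54) = 0.914, a reduction of about 9%.
- √(1 − 0.304 × 0.27) = 0.958, a reduction of about 4%.

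**Chance age imbalance.** On the same assumed gains, age alone contributes a standard error of 0.544 × √(2/389) = 0.039 kg to the difference in raw means.

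**Imbalance from loss, no true effect (all inputs assumed).**

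- By age: 20% infants, gaining 1.0 to 2.0 kg against 0.6 to 0.7 kg in older children, 10% lost in each arm. The same age pattern of loss in both arms gives 0.
- If one arm loses 20% of infants and 7.5% of older children, and the other loses 10% of each, infants make up 0.16/0.90 = 0.178 of the first arm against 0.200 of the second. The difference of 0.022, times a gap in gain of 0.3 to 1.4 kg, is about 0.01 to 0.03 kg.
- If one arm loses only infants and the other only older children, the shares are 0.10/0.90 = 0.111 and 0.20/0.90 = 0.222, and the difference is about 0.03 to 0.16 kg.
- By slower growth of leavers: loss of 5% against 15%, leavers gaining 0.2 to 0.5 kg less, gives (0.15 − 0.05) × 0.2 to 0.5 = 0.02 to 0.05 kg.

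**Scale.** With an assumed SD of gain of 0.5 to 1.0 kg, SD × √(2/389) is 0.04 to 0.07 kg. At design effect 3 it is 0.06 to 0.12 kg. The moderate biases lie below one clustered standard error; the extreme case may exceed it.

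**The case against.** The strongest reply is that missing-weight rules and covariates commonly belong in a statistical analysis plan, which is not at hand, and that two weighings are an ordinary design for a gain outcome. This stands for imputation rules and for the weighing schedule. It does not stand for the test itself, because the protocol names an unadjusted t-test on mean gain as the analysis.

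Next, randomisation protects the comparison without adjustment when loss is unrelated to age or growth, so the main loss is efficiency. That stands, and so does the point that the total gain in precision is modest if clustering is as strong as assumed for diarrhoea.

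A reader might infer that dropping children without an end weight contradicts the intention-to-treat promise. The text does not support this. Analysing children in the arm to which their cluster was allocated is compatible with some missing outcomes, and the protocol nowhere excludes children whose household stops chlorinating.

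A reader might also infer that drop-out biases the weight result. The 10% is a sample-size allowance, not a forecast of missing final weights, and nothing in the document shows that loss would differ between arms. If control households left more often and leavers gained less, the bias would run against the intervention.

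An exit weight with a last-available-weight analysis is open to objection too. It catches only announced departures and mixes exposure lengths, and a single interval term assumes one growth rate at all ages.

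**Conclusion.** The point holds as a matter of efficiency and robustness. For a cohort from birth to under five, the protocol fixes an unadjusted comparison of raw gain where an adjusted one is available from data it already plans to collect.

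The saving is about 14% to 32% of the child-level standard error, and about 4% to 9% of the total if a design effect of 3 applied to weight. Both ranges rest on assumed age mix, gains and standard deviations. A smaller design effect would bring the total saving closer to the first range.

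Bias from differential loss is possible but unproven, and probably small: about 0.01 to 0.05 kg under moderate assumed imbalance. The larger figure of up to 0.16 kg needs each arm to lose a different age group entirely, which nothing in the document suggests. No contradiction with intention-to-treat is established.

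**What to change.** In the Statistical analysis section, replace the t-test on raw gain with a regression of end weight on arm, baseline weight and age at baseline. Allow a non-linear age term, and account for the cluster with a random effect or with GEE grouped by cluster. With baseline weight in the model, the arm coefficient is the same whether the response is end weight or gain, so the result still answers the weight-gain objective.

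State that all children with an end weight are analysed in the arm to which their cluster was allocated, whether or not the household kept using the product. Report the number without an end weight by arm.

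The cost is two or three sentences and a regression in place of a t-test. It needs age recorded in months at the Baseline survey and no further field work. Weighing a child at an announced departure is optional; if done, those weights are better kept for a sensitivity analysis.
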